The Modified Ashworth Scale (MAS) (31, 32) is the most widely used clinical scale to grade spasticity and shows high inter- and intra-rater reliability for the assessment of muscle tone of upper extremities. H reflex can objectively evaluate changes in the excitability of α-motor neurons before and after treatment. Motor nerve conduction velocity (MCV) is a diagnostic technique used to assess peripheral nerve conduction function. By detecting the MCV of the median nerve before and after rESWT intervention, we can observe whether the peripheral nerve has been damaged and determine the safety of the ESWT procedure. Surface electromyography (sEMG) can reflect the overall situation of muscle activity by placing surface electrodes on the muscle to collect electrical signals (33). The sEMG indexes of root mean square (RMS), integrated electromyogram (iEMG), and co-contraction ratio (CR) (34–36) can be used to assess muscle spasms objectively and quantitatively. The MyotonPRO digital muscle function assessment system is a new non-invasive instrument that can be used to evaluate the functional status of skeletal muscles and biological soft tissue. It can quantitatively measure muscle tension, elasticity, stiffness, and other functional conditions (37, 38). A previous study by Dymarek et al. (39) has shown that ESWT can improve trophic conditions of spastic muscles. The infrared thermal imaging (IRT) system detects local trophic condition changes in spasmodic muscles of the upper limbs, which are associated with blood microcirculation and surface temperature distribution (40, 41). The assessment techniques mentioned earlier can reflect the changes of upper limb spasm, muscle tension, nerve excitability, muscle elasticity, and surface temperature of stroke patients from different perspectives and can comprehensively reflect the effects of ESWT from multiple perspectives. Therefore, this trial is designed to use the assessment techniques mentioned earlier to examine the efficacy (rESWT can relieve upper limb spasticity after stroke) and safety (rESWT has no harm to nerve, muscle, and other tissues and organs) of rESWT for the treatment of upper limb spasticity after stroke.

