### Interventions

**Active Radial Extracorporeal Shock Wave Therapy Intervention (Group A):** An rESW device (Power Shocker LGT-2510A, Guangzhou Longest Science & Technology Co., Ltd., China) was used for shock wave therapy. Study participants were treated in the supine position on the area of the biceps brachii, the flexor carpi radialis, and the pronator teres muscle after their affected side has been marked and the skin has been cleaned by soaking with alcohol.

The coupling gel as a contact medium is evenly applied onto the treatment probe to reduce tissue resistance, and a medium- to high-intensity pressure was applied to keep the probe close to each muscle belly. The following protocol is to be used: 2,000 shots, an energy flux density of 0.03 mJ/mm^2^, a pressure of 0.2 MPa (two bars), and a frequency of 8 Hz is delivered to each marked position, for a total of three rounds of treatment, once in 3 days.

**Sham Radial Extracorporeal Shock Wave Therapy Intervention (Group B):** The protocol to be used is the same as that of “group A,” except that pressure is one bar and no coupling gel is used on the treatment site, whereas a thick layer of gauze is placed between the skin and the probe instead, with no pressure applied.

The physiotherapist who is to perform the intervention should have received standardized training and must be familiar with the process and details of the intervention. The patients are all required to undergo the same routine therapeutic program (including common physical therapy and occupational therapy).

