#### Secondary Outcome Measures

Electromyography (EMG), surface electromyography (sEMG), MyotonPRO digital muscle function evaluation system, and infrared thermal imaging (IRT) are to be used for the evaluation.

**H reflex:** H reflex of the median nerve is to be detected using the Schwarzer topas EMG system (Natus Medical Incorporated, Pleasanton, CA, USA). The recording must be conducted from the flexor carpi radialis as follows: the recording electrode is to be placed at the mid-upper 1/3 junction of the medial humeral epicondyle and the radial styloid process line, the reference electrode is to be placed at the tendon, the ground electrode is to be placed at the olecranon, and the stimulation electrode is to be placed at the median nerve proximally to the elbow. The maximal amplitude of H-reflex (H-max) and M-response (M-max) are to be recorded. The H-max/M-max value, which can reflect the excitability change of the α-motor neuron, is to be calculated to detect changes in response to the effect of rESWT on the spasmodic muscle.**Motor Nerve Conduction Velocity:** The same apparatus is to be used, but the electrodes are to be placed differently. The recording electrodes must be placed on the abductor pollicis brevis muscle belly, and the stimulating electrode must be placed on the median nerve at wrist and elbow level to record distal motor latency, MCV, and amplitude. This assessment is aimed at determining whether rESWT causes nerve injury and evaluating its safety.**Root-Mean-Square Value:** An sEMG recording is to be obtained using bipolar Ag/AgCl surface electrodes (MyoMove, Northam Electric Co., Ltd., Shanghai, China) for the sEMG assessment. The patient is to be treated while in a sitting position. The electrodes are to be placed on the fullest part of the upper limbs muscle belly. The locations at which the stimulating and recording electrodes are to be placed must be rubbed with 70% alcohol to reduce skin impedance. Electrode placement is to be done as recommended by Surface EMG Non-invasive Muscle Assessment and the International Society of Electrophysiology and Kinesiology. With the upper limbs of a patient comfortably placed on the treatment table, the resting sEMG activity of the musculus biceps brachii (BM) and flexor carpi radialis are to be measured under stable and static conditions for 30 s at a time. Also, the RMS of biceps brachii and flexor carpi radialis is calculated. RMS can be used to objectively and quantitatively evaluate the condition of muscle spasms, with a higher value indicating a more severe muscle spasm.**Integrated Electromyogram and Co-contraction Ratio:** The patient is seated with the upper body fixed to the seat with a wide nylon strap. The elbow of the patient is at a 45° flexed position and wrist in a neutral position, and the hand holds the handle of the arm strength test joystick of Biodex System 3® dynamometer (Biodex Medical Systems, Shirley, NY, USA). The electrodes are to be placed on the muscle belly of BM and musculus triceps brachii (TM). Training is to be performed for 1 min before the assessment to help patients familiarize themselves with the process. During the test, the patients are to be asked to stretch the elbow joint with maximum strength for 10 s to measure maximum isometric voluntary contraction (MIVC) of TM (44). The iEMG and CR of BM and TM are to be recorded for 20 and 5 s before and after contraction, respectively, as the basic control. The test is to be carried out three times, with an interval of 5 min between each application, and the maximum value is to be recorded. The assessment includes the iEMG of the BM and TM when the elbow is stretched for MIVC, and then the CR is calculated. The iEMG value can reflect the total amount of muscle discharge per unit time and is mainly used to analyze the contraction characteristics of muscles per unit time. CR refers to the proportion of antagonist muscles during the process of active muscle contraction (34), although it is well known that increased synergistic contraction of antagonistic muscles is a common phenomenon in stroke patients. The decrease of CR within MIVC of the elbow indicates a reduction in the strength of the biceps tendon.

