$$\begin{array}{l} \text{CR}=\frac{\text{iEMG of BM }}{\text{iEMG of BM }+\text{ iEMG of TM}}\times 100\% \end{array}$$**MyotonPRO Digital Muscle Function Assessment System:** The MyotonPRO system (Muomeetria Ltd., Tallinn, Estonia, EU) performs a noninvasive measurement of the functional state of skeletal muscles and biological soft tissues, which can quantitatively assess the functional status of muscle tension and elasticity (45, 46). The patient is asked to completely relax while lying in the supine position on a mat, with the forearm in the mid position and the elbow joint extended (if the muscles cannot be fully extended, the forearm is supported on both sides to maintain the forearm neutral position). The measurement point of the BM is tested perpendicular to the skin surface. Measurement is taken once every 1 min, for three times in total, and the average is obtained. The parameters required are (47): F—natural damped oscillation frequency (hertz) to describe muscle tension; C—Creep is the ratio of muscle relaxation time to deformation time, also called Deborah number; R—Muscle internal mechanical pressure release time (millisecond); and C and R reaction to the viscoelasticity of the muscle.**Infrared Thermal Imaging:** A non-invasive and non-contact infrared thermal imaging system (Baotonghua Medical Devices Co., Ltd. Chongqing, China) is to be used to detect changes in local trophic conditions related to blood microcirculation and surface temperature distribution. The instrument has a thermal sensitivity of 0.1 °C. Before measurement, all clothes covering the area to be examined must be removed, and the patients are allowed to adapt to the room for 15–20 min. The room is to be kept quiet with a temperature ranging from 22 to 27 °C and relative humidity below 45%. Then, a thermovision camera is positioned perpendicular to the area of the biceps surface on the anterior side of the arm at a distance of 1 m. The IRT value is obtained in degrees Celsius. The lower the surface temperature, the worse local blood circulation and trophic conditions of muscles.

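### The plan reads a fall in the co-contraction ratio as a weaker biceps, but the ratio as defined cannot show which muscle changed

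*Protocol article*

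**What the plan says.** All of this is in the protocol article.

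- **Definition.** Secondary Outcome Measures, in the paragraph on integrated electromyogram and co-contraction ratio, describes CR as a share: "CR refers to the proportion of antagonist muscles during the process of active muscle contraction". The displayed formula puts biceps (BM) iEMG over the sum of BM and triceps (TM) iEMG, times 100%.
- **Task.** Patients are asked to "stretch the elbow joint with maximum strength for 10 s to measure maximum isometric voluntary contraction (MIVC) of TM". The triceps is thus the agonist and the biceps the antagonist.
- **Reading.** The paragraph ends without any condition: "The decrease of CR within MIVC of the elbow indicates a reduction in the strength of the biceps tendon".
- **Components.** Both signals are taken in the same test: "The assessment includes the iEMG of the BM and TM when the elbow is stretched for MIVC, and then the CR is calculated". Of iEMG the article says: "The iEMG value can reflect the total amount of muscle discharge per unit time". Table 2 lists iEMG and CR as separate items, each at baseline, t1, t2 and t3.
- **Role.** Background groups RMS, iEMG and CR as indexes that "can be used to assess muscle spasms objectively and quantitatively".
- **Concurrent care.** Interventions states: "The patients are all required to undergo the same routine therapeutic program (including common physical therapy and occupational therapy".

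**The concern.** The reading and the formula do not fit together. The sentence assigns every fall in CR to the biceps, yet the triceps signal is in the denominator and moves CR just as readily. The measurement is made during a maximal voluntary effort by the triceps, and that effort can differ from one visit to the next.

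The word strength is a second problem. Surface electrodes on the muscle belly record electrical activity. A ratio of two such recordings says nothing about force, and nothing about a tendon.

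What is at stake is a mechanistic conclusion. Shock waves are applied to the biceps brachii, flexor carpi radialis and pronator teres, not to the triceps, and the Discussion says the trial should clarify the neural and peripheral contributions to spasticity. Under the stated reading, a fall in CR that came from the triceps would be reported as an effect on the treated flexor.

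**Working it through.** **Inputs.** The formula is the article's own. The article gives no iEMG values, so those below are assumed, in arbitrary units. The algebra does not depend on them.

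**Formula.** Write B for biceps iEMG and T for triceps iEMG, both positive.

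CR = 100 × B / (B + T)

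**Direction of change.**
- With T fixed, the derivative in B is 100 × T / (B + T)², which is always positive. A fall in B lowers CR.
- With B fixed, the derivative in T is −100 × B / (B + T)², which is always negative. A rise in T lowers CR.
- Dividing through by T shows that CR depends only on B/T. Multiplying T by k with B fixed therefore gives exactly the same CR as dividing B by k with T fixed.

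**Illustration from B = 40, T = 60.**

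| Change | B | T | CR |
|---|---|---|---|
| Starting point | 40 | 60 | 40/100 = 40.0% |
| Triceps up 50%, biceps unchanged | 40 | 90 | 40/130 = 30.8% |
| Biceps down by one third, triceps unchanged | 26.67 | 60 | 26.67/86.67 = 30.8% |
| Biceps up 25%, triceps up by two thirds | 50 | 100 | 50/150 = 33.3% |
| Biceps up 10%, triceps up 50% | 44 | 90 | 44/134 = 32.8% |
| Both down 20% | 32 | 48 | 32/80 = 40.0% |

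Rows 2 and 3 give the same CR for different reasons. In rows 4 and 5 CR falls although biceps activity has risen. In the last row CR does not move although biceps activity has fallen.

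**Range over starting values.** A triceps rise alone, with the biceps unchanged, lowers CR as follows.

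| Starting CR | Triceps +10% | Triceps +25% | Triceps +50% |
|---|---|---|---|
| 20% | 18.5% | 16.7% | 14.3% |
| 40% | 37.7% | 34.8% | 30.8% |
| 50% | 47.6% | 44.4% | 40.0% |

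The size depends on the assumed values. The direction, and the fact that CR alone cannot separate the two causes, do not.

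**The case against.** The case on the other side has several parts.

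- **Randomisation.** Both arms receive the same routine therapy, so triceps recovery common to both should largely cancel in the comparison of active with sham. This stands. A reader might infer that ordinary rehabilitation gains would be mistaken for a treatment effect; the design does not support that for the between-arm contrast. Two exposures remain: changes read within a group, and a between-arm CR difference that is real but is credited to the biceps when the triceps produced it.
- **The components are recorded.** A reader might also infer that a parallel fall in both muscles would go unseen because CR stays flat. It would not: biceps iEMG is a separately scheduled item at every assessment and would show the fall, and resting biceps RMS is a further measure with no triceps term. This stands too. It makes the correction easy but does not make the sentence right, since no text ties the reading of CR to the component values.
- **Size.** With three sessions once in 3 days and t3 at 24 h after the third, the span from first session to t3 is about 3 + 3 + 1 = 7 days. Nothing in the article shows that triceps activation rises by any given amount in that time. The figures above show what is possible, not what is likely.
- **Only a descriptive sentence.** Statistical Methods has no test or success criterion that depends on it. That limits the weight, but the sentence is an affirmative and unconditional reading, not a detail left to a fuller document.
- **An opposite error.** Labelling every other CR fall as better triceps activation would be just as one-sided. This is right, and the fix avoids it.

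**Conclusion.** The sentence is wrong as written. By the article's own formula CR is a relative share, so a fall shows less biceps activity relative to the total and does not show that biceps activity fell. It shows nothing about strength or a tendon. The conclusion rests on the formula alone; only the illustrative magnitudes are assumed.

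The consequence is limited. CR is a secondary outcome. The Modified Ashworth Scale, the sample size and the primary analysis are unaffected, and no data are lost. What is affected is what the trial may say about the treated flexor, both from within-group changes in CR and from a between-arm CR difference. This is a correction of wording and reporting, worth making before unblinding so that the interpretation is not chosen after the results are seen.

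**What to change.** 1. Replace the closing sentence on CR with: *a decrease of CR indicates a lower relative share of biceps activity (less relative co-contraction) during elbow extension*. Remove the reference to tendon strength.
2. Wherever CR is reported, show the between-arm differences in BM iEMG and TM iEMG from the same contractions beside it.
3. Attribute a CR fall to reduced biceps activity only when BM iEMG is also lower relative to sham. Otherwise report reduced relative co-contraction without assigning it to either muscle.

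The cost is wording and two extra lines in a results table; both signals are already recorded at the same visits. The downside is that fewer CR results will support a biceps-specific claim.

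### Infrared skin temperature is recorded as an absolute value in a room allowed to vary by 5 °C, with no recorded room temperature or reference region named, so avoidable noise enters the change from baseline

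*Protocol article*

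**What the plan says.** The Infrared Thermal Imaging paragraph under Secondary Outcome Measures in the protocol article sets out the measurement in some detail:

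- Environment: "The room is to be kept quiet with a temperature ranging from 22 to 27" (degrees Celsius), with an upper limit of 45% on relative humidity, after clothing is removed and the patient has had 15 to 20 minutes to adapt.
- Region: "a thermovision camera is positioned perpendicular to the area of the biceps surface on the anterior side of the arm at a distance of 1" (metre). No other region is named, on the same arm or the other.
- Instrument: "The instrument has a thermal sensitivity of 0.1 °C".
- Value: "The IRT value is obtained in degrees Celsius".
- Reading: "The lower the surface temperature, the worse local blood circulation and trophic conditions of muscles".

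Table 2 schedules IRT at baseline, t1, t2 and t3. Statistical Methods describes a between-arm comparison of changes from baseline to the end of follow-up, a repeated measures mixed model in secondary analyses, and regressions adjusted for covariates that are not listed. Room temperature appears nowhere in that section.

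**The concern.** After the adaptation period, skin temperature can be expected to follow the room to some degree. A patient imaged at 22 °C at baseline and at 27 °C at t3 may show a warmer biceps without any change in circulation. Subtracting baseline does not cancel this, because the room is a property of the visit and not of the patient.

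The Background assigns IRT to trophic and microcirculatory change, and no other listed outcome measures that. Two things are at stake. Extra visit-to-visit variance can hide a real difference between the arms. And because the article reads the absolute level as a marker of circulation, a rise within a patient or within an arm could be credited to treatment when the room was simply warmer.

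Timing matters too. A covariate can be chosen in a later analysis plan, but a room temperature that nobody wrote down cannot be added then.

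**Working it through.** The article gives no SD, target difference or power for IRT, so there is no IRT figure to reproduce. What follows is a sensitivity calculation.

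**Inputs from the protocol article**
- Permitted room range: 27 − 22 = 5 °C (Infrared Thermal Imaging).
- Patients per arm: 50 randomised, 45 after 10% loss (Sample Size Calculation).
- Two-sided α = 0.05 (Sample Size Calculation; stated there for the responder rate).

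**Assumptions, none of them in the article**
- Room temperature is uniform over the permitted range at each visit.
- Skin responds by *b* = 0.1 to 0.5 °C per °C of room.
- The SD of an IRT change from all other sources is 0.8 °C.
- The true between-arm difference is 0.5 °C.
- The correlation ρ of room temperature between two visits is 0 or 0.5.

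**Step 1: room variation.** SD at one visit = 5/√12 = 1.44 °C. SD of the difference between two visits = 1.44 × √(2(1 − ρ)), which is 2.04 °C at ρ = 0 and 1.44 °C at ρ = 0.5.

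**Step 2: effect on a reading.** The largest shift from the room range alone is 5*b*, or 0.5 to 2.5 °C. The SD added to a change score is *c* = *b* × the step 1 figure. Its share of the variance is *c*²/(*c*² + 0.8²).

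**Step 3: power.** Total SD = √(0.8² + *c*²). Power = Φ(0.5/(total SD × √(2/45)) − 1.96). With no ambient component this gives Φ(2.96 − 1.96) = 84%.

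| *b* | *c*, ρ = 0 | share | power | *c*, ρ = 0.5 | share | power |
|---|---|---|---|---|---|---|
| 0.1 | 0.20 | 6% | 82% | 0.14 | 3% | 83% |
| 0.2 | 0.41 | 21% | 75% | 0.29 | 12% | 80% |
| 0.3 | 0.61 | 37% | 65% | 0.43 | 23% | 74% |
| 0.5 | 1.02 | 62% | 45% | 0.72 | 45% | 60% |

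**Step 4: is it bias or noise?** If room temperature is unrelated to arm, its contribution to the between-arm difference in mean change is centred on zero. Its standard error is *c* × √(2/45): 0.04 °C at *b* = 0.1 and 0.22 °C at *b* = 0.5 with ρ = 0. This adds to the error of the comparison but does not move its centre.

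The loss is negligible at the lowest slope and worth having back from about 0.2 upward if visits are independent.

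**The case against.** The case against has real force on several points.

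- **A reader might infer that IRT is analysed as a raw level.** The article does not support that. It records and interprets the value as an absolute temperature, but Statistical Methods compares changes between randomised arms.
- **A reader might infer a biased treatment effect.** Nothing suggests one. There is a concurrent sham arm, the assessor is described as unaware of grouping, and nothing links room temperature to arm.
- **A 5 °C range is 50 times the 0.1 °C sensitivity.** This is arithmetically true but only descriptive. Sensitivity is neither an error SD nor a target effect.
- **The size is assumed throughout.** The article gives no slope, IRT SD or record of actual room variation. A permitted range is not observed variation, and one patient's post-treatment visits lie close together (first session to t3 is about 2 × 3 + 1 = 7 days), so room temperatures are probably correlated. This stands, and is why the ρ = 0.5 columns are shown.
- **A condensed article may leave covariates to a document not shown.** This stands for the choice of model terms, since the article leaves its relevant covariates open. It carries less weight for data collection. The paragraph is specific about humidity, adaptation time and camera distance, yet describes a single region and no logging of room temperature. No later plan could adjust for a value that was not collected. The full protocol may provide for logging; if so, only the model term remains to be settled.
- **IRT is one secondary outcome among several** and plays no part in the sample size. This stands and limits the priority.

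**Conclusion.** The point holds as a cheap improvement. Differences in room temperature between visits enter the IRT outcome and survive subtraction of baseline, and the article names neither a recorded room temperature nor a reference region with which to remove them. The consequence is avoidable noise in one secondary outcome, and within-arm changes that cannot be separated from room changes. It is not evidence of bias between the arms, and it does not touch the primary outcome.

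The added SD of a change score is 0.20 to 1.02 °C with independent visits, and less with correlated ones. In the illustration this means power of 82% to 45% in place of 84%, or 83% to 60% at a correlation of 0.5. The width of these ranges shows that the true size is unknown. The conclusion rests on the direction of the effect and the low cost of removing it, not on any single figure.

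**What to change.** 1. Record the actual room temperature at every IRT session from now on, and recover room logs for patients already imaged where such logs exist.
2. Include room temperature as a time-varying covariate in the mixed model for IRT. Treatment does not affect it, so adjusting for it is safe. Where earlier readings are missing, show the unadjusted result for all patients beside the adjusted one.
3. Base IRT conclusions on the between-arm contrast. Do not read a within-arm rise in absolute temperature as improved circulation.
4. An affected-minus-unaffected arm difference may be added as a supportive analysis only. It brings in the measurement noise of a second region, and it gains precision only if the two arms move together closely enough, which has not been shown.

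The cost is one thermometer reading per session and one model term. The main downside is coverage: Trial Status reports 50 of the planned 100 patients recruited at submission, so without recoverable logs the gain in precision may apply to about half the sample. Treatment, eligibility, the primary outcome and the sample size are unchanged.
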